**Table of Correlation Evaluation Criteria for Adverse Events and Drug Use**

|  | Definitely related | Probably related | Probably unrelated | Definitely unrelated | Unjudged |
| --- | --- | --- | --- | --- | --- |
| Have a reasonable chronological order with the study drug | ＋ | ＋ | ＋ | － | ? |
| For the known reaction type of the study drug | ＋ | ＋ | － | － | ? |
| Explanation for reasons other than available research equipment | － | ± | ± | ＋ | ？ |
| Responses lessen after decompression of study drug | ＋ | ± | ± | － | ? |
| The reaction reappears after the study drug is reused | + or ? | ? | ? | － | ? |

Note: "+" in the table is affirmative; "-" is negative; "±" is difficult to affirm or deny; "?" indicates that the situation is unknown.

**Severity Criteria**

Severity should be assessed according to the following graded descriptions:

• Mild: No symptoms or discomfort; does not interfere with daily activities and function; usually does not require medication to relieve symptoms.

• Moderate: Symptoms cause significant discomfort; daily activities and function are affected; study participation can be continued; intervention required to relieve symptoms.

• Severe: Severe causes severe discomfort; symptoms result in loss of function and significantly interfere with daily activities; in severe cases, study drug can be discontinued; symptomatic treatment and/or hospitalization are required.

The investigator should use clinical judgment to assess the severity of the event (e.g., abnormal laboratory results) from the subject's direct experience.

**7.3 Safety report**

**All adverse events**

All adverse events, regardless of their severity, nature of severity, or their causal relationship to study drug, from the time of signed informed consent until the last follow-up visit (90 days after randomization), are to be recorded in medical terms on the clinical research form. When symptoms and signs are caused by common causes, a diagnosis of the disease should be given where possible (e.g., cough, runny nose, sneezing, sore throat, and headache should be reported as "upper respiratory tract infection"). The investigator must make a judgment on the causal relationship between the adverse event and the study drug and record it on the clinical research form. All drugs for adverse events should be documented in the original medical record and reported as requested by the sponsor.

All serious adverse events in clinical research must be reported to the ethics committee of the centre, the principal investigator of the centre, the sponsor, the contract research organization, the research team leader unit, and the adverse reaction monitoring centre within 24 hours; Report to the ethics committee and data and safety monitoring committee of the team leader unit within 7 natural days after being informed. Investigators must complete a serious adverse event form to record the time, severity, duration, actions taken and outcomes of serious adverse events. Any follow-up information for serious adverse events should also be reported in writing within 24 hours according to the above process.

All serious adverse events that do not resolve at study termination or subject early withdrawal must be followed up to any of the following:

- 1. Incident mitigation
  2. Events are stable
  3. If the baseline value is known, the event returns to the baseline value
  4. Events can be attributed to other treatments or factors not related to study
  5. It is unlikely that any further information will be available (subject or physician refuses to provide further information and remains lost to follow-up after various follow-up attempts)

**Death**

Death is the result of an event. The death of a subject in a clinical trial, regardless of whether the event is expected or treatment-related, would be considered a serious adverse event. Events leading to death should be recorded in medical terms and reported on the eCRF. All causes of death (death diagnoses) must be reported as serious adverse events. Investigators should make every effort to obtain and send death certificates and autopsy reports to designated personnel.

**Pregnancy**

If the researcher finds that the subject is pregnant during the research, the researcher should fill out the "Pregnancy Incident Report Form" within 24 hours after learning and report it to the clinical research supervisor, and notify the project leader by phone

Abnormal pregnancy results, considered serious adverse events, should be reported in accordance with the Serious Adverse Event Reporting Procedure.

**Abnormal laboratory test results**

During the course of the study, when the results of laboratory tests meet the following conditions, they must be regarded as adverse events and recorded in medical terms on the adverse events of the CRF:

1. Accompanying clinical symptoms
2. Causing a change in the trial protocol (eg treatment interruption or discontinuation)
3. Leading to a change in medical intervention or concomitant treatment
4. Clinically significant as judged by the investigator (medical and scientific methods should be used to judge whether an isolated laboratory abnormality is an adverse event)

When the adverse event meets the serious criteria, it should be reported in accordance with the serious adverse event reporting procedure.

**7.4 Data Safety Monitoring Committee (DSMC)**

An independent DSMC will be chaired by a neurologist, and include two neurologists and an independent statistician. DSMC will perform data verification every six months in this study. DSMC will recommend to terminate or continue the trial. The primary purpose of the termination is to protect the rights and interests of the patients and to avoid unnecessary economic losses.

**8. Statistics**

**8.1 Sample size**

Given that this was a pilot, single-arm study, no formal sample size calculation was performed. A total of 30 patients was set based on the recommendation of the Steering Committee.

**8.2 Statistical analysis plan**

Student’s t-test or Mann-Whitney U test will be used for comparison of continuous variables based on their normality, and Pearson 's χ² test will be performed for categorical variables. To compare the outcomes between two groups, logistic regression model will be used for the analyses of 90-day mRS, early neurological improvement, symptomatic intracranial hemorrhage and intracranial hemorrhage, generalized linear model for change in NIHSS score, and COX regression model for mortality at 90 days. To minimize bias in the group comparison, we will perform propensity score matching (PSM) and inverse probability of treatment weighting (IPTW) analysis accounting for multiple confounders. Propensity score (PS) will be calculated using a logistic regression model adjusted for age, baseline NIHSS, pre-treatment with IVT, MT passes and occlusion location, and performed 1:1 PSM based on the nearest-neighbor matching with a caliper width of 0.2 of the standard deviation of PS. IPTW will be estimated based on the PS to create a synthetic sample with baseline characteristics independent of treatment assignment, and further conducted IPTW-weighted analysis. All statistical analyses will be performed using SPSS software (version 25.0) and R software (version 4.3.2), and two-sided test with *P*<0.05 will be considered statistically significant.

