**3. Design and selection of patients**

**3.1 Trail plan**

This is a prospective, pilot, single-arm, open label, blinded endpoint, and single centre trial.

All enrolled patients will receive intra-arterial administration of argatroban (0.2-0.3 mg/min), dexamethasone (0.1 mg/min) and edaravone (0.3 mg/min) for 30 to 60 minutes after successful recanalization. In addition, all patients will receive standard medical care as per national stroke guidelines.

Follow-up will be performed at baseline, 48±12 hours, 10 ± 2 days, and 90 ± 7 days, respectively.

All clinical assessments including NIHSS and mRS will be evaluated by certified assessors according to a standardized procedure manual. The primary endpoint (mRS at 90 days) will be mainly evaluated, in person or by telephone interview (if in person interview is not possible), by one trained and certified staff.

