**5. Treatment administered to included subjects**

**5.1 Description of the treatment required to conduct the study**

All enrolled patients will receive intra-arterial administration of argatroban (0.2-0.3 mg/min), dexamethasone (0.1 mg/min) and edaravone (0.3 mg/min) for 30 to 60 minutes after successful recanalization. In addition, all patients in the intervention arm will receive standard medical care as per national stroke guidelines.

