**6. Outcome measurements**

**6.1 Primary efficacy outcome**

Proportion of mRS (0–2) at 90±7 days after randomization.

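### Section 8.2 plans only two-group analyses, but the trial has one arm and defines no comparator, so the named analysis of the primary outcome cannot be run on the data collected

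*Protocol*

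**What the plan says.** Protocol section 3.1 states the design: "This is a prospective, pilot, single-arm, open label, blinded endpoint, and single centre trial". Section 5.1 gives every participant the same treatment: "All enrolled patients will receive intra-arterial administration of argatroban", together with dexamethasone and edaravone. Section 8.1 fixes the size without a calculation: "Given that this was a pilot, single-arm study, no formal sample size calculation was performed", and "A total of 30 patients was set based on the recommendation of the Steering Committee". Section 6.1 defines the primary outcome as one proportion: "Proportion of mRS (0–2) at 90±7 days after randomization".

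Section 8.2 is written for a different design. It names t-tests or Mann-Whitney tests and chi-square tests. It then says: "To compare the outcomes between two groups, logistic regression model will be used for the analyses of 90-day mRS". The same logistic approach covers early neurological improvement, symptomatic intracranial haemorrhage and any intracranial haemorrhage. A generalized linear model is named for NIHSS change and a Cox model for 90-day mortality. It continues: "To minimize bias in the group comparison, we will perform propensity score matching (PSM) and inverse probability of treatment weighting (IPTW) analysis". The matching is specified as "performed 1:1 PSM based on the nearest-neighbor matching" with a caliper of 0.2 standard deviations of the score. Two-sided P<0.05 counts as significant.

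**The concern.** Every inferential method in section 8.2 contrasts a treated group with an untreated one, and the protocol enrols only treated patients. No source, calendar period, eligibility rule, time zero, size or outcome method is given for any other group. The primary outcome is a single proportion, but the only method attached to it is a between-group regression.

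The text can be followed only if a comparator is added afterwards. The choice of controls could then drive the result, and the comparison would carry P values under a prespecified heading although its main design element was never specified. The primary objective (section 2.2) points the same way: it speaks of testing an improvement in functional outcome, which needs a reference that the design does not contain.

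**Working it through.** **No planned figure to reproduce.** Section 8.1 gives no power, effect size or reference rate behind the 30 patients.

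**Inputs from the protocol.** One arm (3.1); all enrolled patients treated (5.1); n = 30 (8.1); primary outcome a single proportion (6.1); propensity model on age, baseline NIHSS, prior intravenous thrombolysis, thrombectomy passes and occlusion location (8.2).

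**Step 1: can the methods of 8.2 be run on these data?** Let T be the treatment indicator. Here T = 1 for all 30 patients.
- Outcome model: logit P(Y = 1) = a + bT. With T always 1, only the sum a + b is identified; b, the group effect, is not. The group coefficient in the Cox model fails for the same reason.
- Propensity score: e(x) = P(T = 1 | x). With no T = 0, the likelihood pushes every fitted score towards 1 and has no finite maximum. A trial logistic fit with 30 treated patients and five simulated covariates ended in perfect separation and a singular matrix.
- 1:1 matching: untreated candidates = 0, so matched pairs = 0.
- Inverse probability weighting: control weights 1/(1 − e) apply to nobody.
- t-test, Mann-Whitney and chi-square: the second sample is empty.

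**Step 2: what can 30 patients support?** The exact (Clopper-Pearson) 95% limits for x events in n patients are
- lower = 2.5th percentile of Beta(x, n − x + 1)
- upper = 97.5th percentile of Beta(x + 1, n − x)

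| Illustrative result | Proportion | Exact 95% interval |
|---|---|---|
| mRS 0–2: 14/30 | 46.7% | 28.3% to 65.7% |
| mRS 0–2: 15/30 | 50.0% | 31.3% to 68.7% |
| mRS 0–2: 18/30 | 60.0% | 40.6% to 77.3% |
| mRS 0–2: 20/30 | 66.7% | 47.2% to 82.7% |
| sICH: 0/30 | 0% | 0% to 11.6% |
| sICH: 2/30 | 6.7% | 0.8% to 22.1% |

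At 15/30 the half-width is (68.7 − 31.3)/2 = 18.7 points. For 0/30 the upper limit is 1 − 0.025^(1/30) = 0.116. The counts are examples, not predictions.

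**Step 3: if a comparator were added.** Assume that 1:1 matching found a control for every patient, giving 30 v 30, with both proportions near 50%. Treating the groups as independent, the half-width of the 95% interval for the risk difference is 1.96 × √(0.5 × 0.5/30 + 0.5 × 0.5/30) = 1.96 × √0.01667 = 0.253, or about ±25 points. This applies to the matched analysis only, since weighting does not limit the controls to 30.

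**The case against.** **A separate statistical analysis plan may exist.** It could properly hold the interval method and the choice of main estimate among unadjusted, matched and weighted results, and their absence here is not counted as a fault. But whether a trial has a comparator, and which one, is a design decision. Such a plan could carry out 8.2 only by bringing in a group that the protocol does not contain.

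**An external cohort may have been intended.** The propensity covariates fit a series of thrombectomy patients, and the methods would become runnable if such a series were defined. That is fair, but no readable text defines one. The study-procedure figure in section 6.5 is not shown, so its content is unknown; sections 3.1 and 8.1 make it unlikely that it holds a control group. Other wording, such as timing from randomization (6.1) and the reference to an intervention arm (5.1), would equally fit text carried over from a controlled design.

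**Stronger readings that a reader might infer:**
- That the primary outcome has no analysis at all. Section 8.2 does name logistic regression for 90-day mRS, and section 6.1 fixes the point estimate as a proportion. What is missing is a named analysis that this design can execute.
- That controls have been, or will be, picked with their outcomes known. Nothing in the protocol says so. The text leaves this open, and no more can be claimed.
- That a false-positive rate can be computed by multiplying outcomes by methods. Section 8.2 names six outcomes, but estimates of one outcome by three methods on overlapping patients are strongly correlated, so a figure based on independence would mislead. Section 6.1 also designates one primary outcome.
- That the comparison has a known low power against the 46.0% in the Background. That rate comes from a population with about 80% recanalization, whereas this trial requires mTICI 2b–3. The protocol does not adopt it as a benchmark, and it states no target effect.

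**Conclusion.** The point holds and must be corrected. The protocol contradicts itself: sections 3.1, 5.1 and 8.1 describe one treated arm of 30, and section 8.2 prescribes only between-group methods with no group to compare against. The analysis named for the primary outcome is therefore not executable on the data collected.

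This conclusion needs no numerical assumption. It rests on the readable text, with the caveat of the missing figure in section 6.5. The sizes are secondary: about ±19 points for a single proportion near 50%, and about ±25 points for a risk difference if matching yielded 30 v 30, which is an assumption. No stated number in the protocol is shown to be wrong, and 30 patients are not shown to be too few for a pilot that estimates rather than tests.

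**What to change.** 1. **Primary analysis (8.2).** Report the number and proportion with mRS 0–2 at 90 days among all patients in whom the infusion was started, with an exact Clopper-Pearson 95% interval.
2. **Other outcomes.** Do the same for mRS 0–1, early neurological improvement, symptomatic intracranial haemorrhage, any intracranial haemorrhage and 90-day death. Summarise NIHSS change within the arm with a 95% interval.
3. **Population.** State that the elimination criteria in section 3.2 (such as no laboratory record, or use of a prohibited treatment) do not remove treated patients from this analysis.
4. **Objective (2.2).** Reword it from testing an improvement to estimating functional outcome and safety. Otherwise removing the comparison leaves an objective that cannot be tested.
5. **Two-group text.** Either delete the group comparison, matching and weighting, or move them to a section labelled exploratory. In the second case define the external cohort before any control outcome is seen: source, calendar period, the same eligibility, time zero, the same 90-day mRS method, and one adjusted estimate named as the main one.

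Items 1 to 4 and the deletion option change wording only, with no added patients or procedures. The exploratory option has the cost of finding and assembling control data with comparable 90-day assessment, and its P values would not be confirmatory.

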**6.6 Study periods**

**Screening period:** On day 0 (baseline period), it is necessary to complete enrolment screening, and collect demographic characteristics, medical history (including history of hypertension, diabetes and drug treatment history), brain imaging (computer tomography, computed tomography angiography or magnetic resonance imaging), neurological measurements (NIHSS score, mRS score), hematological examination (blood routine, blood glucose, hepatic and renal function, coagulation routine, urine routine, electrocardiogram, etc) and other information.

**Treatment period:** All enrolled patients receive intra-arterial drugs. The perioperative data including time and dose of intra-arterial drugs, LVO recanalization time, mTICI grade, etc. will be recorded and cranial CT will be performed immediately after the procedure.

**Follow-up period:** NIHSS score will be assessed at 48±12 hours, and 10 ± 2 days. Repeated brain CT will be performed at 48±12 hours. The mRS score will be assessed at 90 ± 7 days. All concomitant medications, adverse events, stroke recurrence and other vascular events of each visit will be recorded since the last visit.

All the adverse events of included subjects should be recorded and tracked until properly resolved.

All the serious adverse events of included subjects should be recorded and tracked, even if the subjects have finished the trial, until the events are resolved, or stabilization judged by the investigator.

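### Section 8.2 names baseline NIHSS for the propensity score but not for the NIHSS-change model; if a group comparison is kept, it belongs in that model too (minor)

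*Protocol*

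**What the plan says.** Section 8.2 sets out a comparison between two groups. For NIHSS the response is a change score, analysed with a "generalized linear model for change in NIHSS score". No covariates are listed for this model, nor for the logistic and Cox models named in the same sentence.

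Baseline NIHSS appears once in the section, in the propensity score, which is "adjusted for age, baseline NIHSS, pre-treatment with IVT, MT passes and occlusion location". Against confounding, "we will perform propensity score matching (PSM) and inverse probability of treatment weighting (IPTW) analysis accounting for multiple confounders". The matching rule is "1:1 PSM based on the nearest-neighbor matching with a caliper width of 0.2 of the standard deviation of PS", and a "two-sided test with *P*<0.05 will be considered statistically significant".

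The data are available for enrolled patients. Section 6.6 collects "neurological measurements (NIHSS score, mRS score") at screening and then states that "NIHSS score will be assessed at 48±12 hours, and 10 ± 2 days". Section 3.2 sets no NIHSS limits for entry.

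Three other facts bear on the weight of the point. Section 3.1 describes a single-arm trial, and no second group is defined anywhere. Section 8.1 sets 30 patients without a formal calculation. Sections 6.1 to 6.3 do not list change in NIHSS as an outcome; NIHSS enters there only through early neurological improvement and the definition of symptomatic haemorrhage.

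**The concern.** A change score treats each point of baseline NIHSS as worth exactly one point at follow-up. If the true slope is below 1, patients who enter with higher scores tend to show larger falls whatever their treatment. A patient who enters at 6 can fall by at most 6, and one who enters at 20 by up to 20. Groups that were not randomised may well differ at entry, and a crude comparison of change would then credit part of that difference to the treatment. Even with no imbalance, an unadjusted change score is noisier than a baseline-adjusted analysis.

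Baseline NIHSS is already measured in the treated patients and already required by the propensity score. Using it in the outcome model as well costs one degree of freedom.

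**Working it through.** The protocol gives no NIHSS SD, correlation, effect size or comparator size, so there is no stated figure to reproduce. Every input below except the 30 treated patients, the two-sided 0.05 level, the five propensity-score covariates and the 0.2 SD caliper is an assumption. Section 8.2 does not say which follow-up visit the change refers to, which is a further reason to show a range for rho.

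**1. Bias of the crude change score.** With equal SDs at both times, the slope of follow-up on baseline is rho. If the treated group enters D points higher, the expected difference in change with no treatment effect is (rho − 1) × D. Per point of imbalance that is −0.7, −0.5, −0.3 and −0.1 at rho 0.3, 0.5, 0.7 and 0.9. For D = 2 and rho 0.5 it is −1.0 point. Simulation (SD 6, 30 treated, 1,500 runs) gave −0.98 with 30 controls and −1.03 with 120; adding baseline gave 0.02 and −0.03. With D = 0 there is no bias.

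**2. False positives in the crude analysis.** Take 30 treated, 90 controls and D = 0.4 SD. In SD units, bias = 0.4(1 − rho) and SE = √[2(1 − rho)] × √(1/30 + 1/90).

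| rho | bias | SE | bias/SE | two-sided rejection rate |
|---|---|---|---|---|
| 0.3 | 0.28 | 0.249 | 1.12 | 20% |
| 0.5 | 0.20 | 0.211 | 0.95 | 16% |
| 0.7 | 0.12 | 0.163 | 0.73 | 11% |

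Four simulations with 30 treated and five covariates, differing in selection strength, gave 21–30%, 17–23% and 13–15%. Where the model with baseline was also run, it gave about 3–5%.

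**3. Precision of the crude analysis with no imbalance.** Var(change) = 2(1 − rho)s² and Var(adjusted) = (1 − rho²)s², so the ratio is (1 + rho)/2: 0.65, 0.75, 0.85 and 0.95 at rho 0.3, 0.5, 0.7 and 0.9. Where the adjusted model has 80% power, the change score has about 62%, 68%, 73% and 78%.

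Example at rho 0.5, SD 6 and 30 per group: the difference detectable with 80% power is 2.80 × 6/√15 = 4.34 points for change, and 2.80 × 5.20/√15 = 3.76 points adjusted.

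**4. Matched and weighted analyses.** With baseline NIHSS as the only propensity-score covariate, bias was about 0 under both methods. The sampling SD was the same with and without a baseline term under matching (1.60 and 1.60 with 30 controls and no imbalance) and nearly so under weighting (1.35 and 1.36).

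Section 8.2 specifies five covariates, which makes the match on NIHSS itself looser. The SD of the residual baseline imbalance rose from 0.01 to about 0.14 SD. With 30 treated, 90 controls and an effect of 0.65 SD, matched power without and with the baseline term in three runs was:

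| rho | run A | run B | run C | gain |
|---|---|---|---|---|
| 0.3 | 48→65% | 48→64% | 50→64% | 14–17 |
| 0.5 | 65→76% | 68→77% | 64→77% | 9–13 |
| 0.7 | 83→87% | 85→89% | 83→86% | 3–4 |

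A fourth run of similar design gave 51→66%, 65→74% and 83→88%.

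**5. Where the matched gain comes from.** In run B at rho 0.3, the true sampling SD fell from 0.285 to 0.268, but the SE reported without the baseline term was 0.324. If both analyses had used their true sampling SD, power would be Φ(0.65/0.285 − 1.96) = 63% and Φ(0.65/0.268 − 1.96) = 68%, a gain of about 5 points. The rest comes from the reported SE being too large without the term; with it, the SE was 0.266, close to 0.268. In run C most of the gain remained with pair-clustered standard errors.

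**6. Weighting with a robust SE.** Power rose from 62% to 77%, 77% to 85% and 89% to 93% at rho 0.3, 0.5 and 0.7. With the term added the false-positive rate was 7–8%, so part of that gain is not real unless the SE allows for the estimated weights.

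**The case against.** The strongest objection is that the omission is read from silence. Section 8.2 lists no covariates for any outcome model, a generalized linear model can carry a baseline term, and a separate analysis plan that is not shown may supply one. This stands as far as it goes: a reader might infer that the protocol excludes baseline NIHSS from the model, and the text does not say so. What the section does fix is a change score as the response and a single named role for baseline NIHSS, in the propensity score. The point is an improvement to that choice and does not rest on missing detail.

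The second objection is that the section already deals with the bias. That is correct for the matched and weighted analyses. A reader might infer that every group comparison is biased, or that every one loses appreciable power. The calculations support neither: the bias belongs to the crude comparison only, and it needs both a baseline imbalance and a slope below 1, neither of which the protocol gives. At high rho there is little to gain.

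Third, the matched gain depends partly on the variance estimator, and the protocol names none. This stands in part. The improvement in the estimator itself is smaller than the gain in tested power, although most of the latter remained with pair-clustered standard errors.

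Fourth, the analysis is peripheral and has no defined second group. This stands in full and sets the severity. A reader might also take it that baseline NIHSS is collected on every patient compared; the protocol documents it only for the 30 enrolled.

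**Conclusion.** The point holds as a minor, conditional improvement. If a two-group comparison of NIHSS change is kept, the crude analysis without a baseline term carries (1 − rho) times any baseline imbalance into the estimate and has a variance 1/0.65 to 1/0.85 times that of the adjusted analysis at rho 0.3 to 0.7. In the matched and weighted analyses the bias is already removed. The remaining benefit is power: in the matched analysis roughly 10 to 15 points at rho 0.3 to 0.5, about 3 to 5 at rho 0.7, and little beyond that.

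These sizes rest on assumed correlation, equal SDs, pool size, selection strength and effect size. The primary outcome and the listed secondary and safety outcomes are not affected by how this model is specified. The missing comparator is the larger problem in section 8.2, and resolving it may remove this model altogether.

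**What to change.** In section 8.2, replace the NIHSS clause with: 'linear model for follow-up NIHSS (or change from baseline) with baseline NIHSS as a covariate'. Apply it to the crude, matched and IPTW-weighted analyses alike. State that standard errors will allow for the matching or for the estimated weights, for example by bootstrap for the weighted analysis.

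With baseline in the model, follow-up NIHSS and change give the same treatment estimate in a linear model, so either response will do. If a comparator is defined, confirm that baseline NIHSS is available for it. If none is defined, delete this model.

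The cost is one sentence and one degree of freedom. Nothing new has to be collected on the enrolled patients, and any comparator must supply baseline NIHSS anyway for the propensity score.

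### If the two-group comparison is kept, ordinary logistic regression does not suit symptomatic intracranial haemorrhage in 30 treated patients, and the propensity score leaves out two recorded reperfusion factors

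*Protocol*

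**What the plan says.** Section 3.1 fixes the design: "This is a prospective, pilot, single-arm, open label, blinded endpoint, and single centre trial". Section 8.1 states that "no formal sample size calculation was performed" and then "A total of 30 patients was set based on the recommendation of the Steering Committee". No section names a control group, its source or its size.

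Section 8.2 nevertheless plans a comparison: "To compare the outcomes between two groups, logistic regression model will be used for the analyses of 90-day mRS, early neurological improvement, symptomatic intracranial hemorrhage". It names no exact or penalised method for sparse outcomes. Section 6.3 lists sICH within 48±12 hours as the only safety outcome.

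For adjustment, section 8.2 says "Propensity score (PS) will be calculated using a logistic regression model adjusted for age, baseline NIHSS, pre-treatment with IVT, MT passes and occlusion location". These five covariates feed both a 1:1 matched analysis and inverse probability of treatment weighting (IPTW), the latter meant to "create a synthetic sample with baseline characteristics independent of treatment assignment".

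Section 6.6 lists among the procedural data that "LVO recanalization time, mTICI grade, etc. will be recorded". Section 3.2 makes both items part of eligibility: mTICI 2b-3, reached within 7 hours of onset. Neither is in the propensity score.

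**The concern.** Two choices written into section 8.2 look ill-suited to the data the trial will produce.

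The first is the model for sICH. Maximum-likelihood logistic regression needs events in both groups. With 30 treated patients and an uncommon event, a treated group with no events is a realistic result, and it is also the best safety result the trial could have. The named model cannot summarise it with a usable estimate and interval. Matching and weighting do not help: no events among the treated remains no events after either.

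The second is the covariate list. The case for the cocktail in section 1 rests on the gap between recanalization and functional outcome. Reperfusion grade and delay are therefore obvious candidates for confounding, and the score ignores both. The protocol does not say that comparison patients must meet the same mTICI and 7-hour criteria. A difference between groups in either factor could be read as an effect of treatment.

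**Working it through.** The protocol gives no sICH rate, effect size or power, so it has no figure to reproduce.

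**Inputs.** Treated patients: 30 (section 8.1). Rate of mRS 0-2 after thrombectomy: 46.0% (section 1). sICH rate: assumed 5%, range 3% to 8%. Control numbers: assumed, because none are stated.

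**1. Expected treated sICH events, 30 × p**
- 3%: 0.9
- 5%: 1.5
- 8%: 2.4

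**2. Chance of no treated event, (1 − p)^30**
- 3%: 0.97^30 = 0.401
- 5%: 0.95^30 = 0.215
- 8%: 0.92^30 = 0.082

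In these cases the estimated odds ratio is 0, its logarithm is not finite, and the Wald standard error and interval are unusable.

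**3. Chance of an empty event cell in either group, if there were 30 controls at the same rate, 2q − q² with q from step 2**
- 3%: 0.802 − 0.161 = 0.641
- 5%: 0.429 − 0.046 = 0.383
- 8%: 0.164 − 0.007 = 0.157

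With larger control groups this falls towards the step 2 figures, which are the floor.

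**4. What an exact interval gives for 0/30.** Lower limit 0; upper limit 1 − 0.025^(1/30) = 0.116. The result is 0% to 11.6%.

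**5. The primary outcome, for contrast.** 30 × 0.46 = 13.8 expected patients with mRS 0-2. An unadjusted logistic model is estimable here, though imprecise.

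**6. Omitted covariates.** A simulation with no true treatment effect used 30 treated patients, 30, 60, 120 or 300 controls, 300 runs per setting, and one prognostic factor left out of the score. Confounder strengths were assumed.
- Factor differs between groups, score without it: mean bias in the mRS 0-2 risk difference +0.05 to +0.08.
- Same settings, factor added: about −0.02 to +0.01. The standard deviation of the estimate rose by 0.001 to 0.018.
- Factor does not differ (120 controls), score without it: bias 0.003.

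The standard deviation of a single estimate was 0.10 to 0.14 without the factor, so the bias is smaller than the sampling error of one such study.

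**7. Load on the score.** Treated patients per covariate: 30/5 = 6 as planned; 30/7 = 4.3 with the two reperfusion factors; 30/8 = 3.75 if pre-stroke mRS is also added.

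**The case against.** The strongest reply is that the point depends on a comparison the trial cannot make as designed. With no control group defined, the size of any confounding cannot be fixed from the protocol. Section 2.4 only asks for the occurrence of sICH, which a proportion answers. This stands, and it is why the point is conditional. But section 8.2 names sICH among the outcomes to be compared by logistic regression, so the choice of model is stated rather than left open.

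On the covariates, section 3.2 already confines enrolled patients to mTICI 2b-3 within 7 hours, which limits variation without removing it. Section 6.6 records these items for trial patients, and nothing shows that controls would have them. More covariates also strain a score built on 30 treated patients. All of this stands and shapes the fix.

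A reader might infer more than the documents support:
- **That the named models fail in general.** They do not: logistic regression for mRS 0-2 is estimable.
- **That sICH is to be tested by Pearson chi-square, and invalidly.** Section 8.2 gives chi-square for categorical variables generally and assigns sICH to the logistic model, so this use is an inference. The expected treated count would reach 5 only at a pooled rate of 5/30 = 16.7%. Even so, the test's exact size at assumed rates of 2% to 10% was mostly 3.5% to 5.4% (extremes 0.3% and 7.3%).
- **That IPTW must be replaced.** In simulation the median effective number of treated patients was 19 to 27 of 30, and the largest single weight was 7% to 12% of the treated total at the median. Tails were worse (5th percentile of effective size 9 to 21; largest weight up to 27% at the 95th percentile). That is lost precision, not collapse. The target population is a choice of estimand, the gain from changing it depends on an undefined control pool, and the planned 1:1 matching already targets patients like those treated.
- **That the adjusted results would be confounded.** Step 6 shows this only if the omitted factors differ between groups.
- **That prior disability is recorded and ignored.** The mRS is taken at screening, and note 1 to the flow chart in section 4.1 places day 0 after stroke onset. Nothing says the score refers to pre-stroke status.

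**Conclusion.** The point holds in a limited, conditional form. If the two-group comparison is kept, ordinary logistic regression without a sparse-data alternative is the wrong tool for sICH: the chance of no treated event among 30 is 21% at an assumed 5% rate, 40% at 3% and 8% at 8%. These figures rest on the assumed rate, not on the unknown controls.

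The covariate point is secondary. Final mTICI grade and onset-to-recanalization time define eligibility and can be obtained from recorded data, yet the score omits them. Bias is possible rather than shown, and its size cannot be set from the protocol. The lack of any defined comparison group remains the more basic fault in section 8.2.

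**What to change.** First define the control source and its eligibility, or drop the comparison. Then amend section 8.2 as follows.

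- **sICH:** report the count and proportion with an exact (Clopper-Pearson) 95% interval, whether or not there is a comparison. If groups are compared, use Fisher's exact test or Firth-penalised logistic regression with few covariates. Apply the same rule to any other outcome with few events.
- **Propensity score:** add final mTICI grade (2b against 3) and onset-to-recanalization time where controls have both, and fit the score with penalisation. If controls lack them, say so as a limitation.
- **mRS at screening:** state whether it means pre-stroke status. Add it to the score only if it does.
- **IPTW:** no replacement is needed. At most, report covariate balance and effective sample size beside the weighted result.

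The cost is wording and a few lines of analysis code. Two more covariates may slightly reduce overlap and precision with 30 treated patients. Fisher's test is conservative at these counts: with 30 controls its exact size was below 1% at assumed rates of 2% to 10%. The exact interval should therefore carry the safety message.
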